#### Qualitative

Content analysis [42] and thematic analysis [43] will be undertaken to determine the major categories in the qualitative data (acceptability FGDs and KIIs). Recordings will be translated verbatim to English and transcribed. An inductive approach will then be employed to analyze the recordings of FGDs and KIIs. Codes will be generated as part of the initial review process and entered into a standardized extraction table. Coded data will then be examined for key themes. Themes will be categorized using thematic maps to identify key and shared concepts across themes. Once organized, themes will be reviewed and defined, and key extracts identified. Acceptability and KAP qualitative data will first be examined separately, and then reviewed together to identify shared themes.

All statistical analyses will be performed using IBM SPSS (IBM SPSS Inc), Stata (StataCorp) or SAS software (SAS Institute Inc). Microsoft Excel, and NVivo (QSR International) will be used for qualitative analyses.

### Power

The sample size was calculated to achieve 80% power, assuming baseline knowledge of 30 percentage points (as reported in the original “Magic Glasses” intervention by Bieri et al [31]) and a design effect of 2 to account for cluster sampling. Accounting for 10% attrition, it was estimated that a total of 227 participants would be needed to detect a difference of 5 percentage points in knowledge between intervention and control groups. As such, we will aim to enroll a total of 228 schoolchildren in years 3-5 (114 in intervention arm, 114 in control arm) in each country.

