### Consent and Recruitment

Based on local expertise on school student numbers in each country, approximately 6 schools will be selected in each country to achieve a total sample size of 228 per country. Prospective schools will be selected in consultation with the local departments of education. Once schools are identified, permission to conduct the study will be sought from the principal of each selected school. Teachers and parents or legal guardians of prospective participants will then receive an information sheet outlining the procedure and purpose of the study and contact information, and a consent form. On receiving the written parental or guardian consent, the aims, process, and outcome of study will be explained to prospective student participants and their written assent will be sought. Only schoolchildren who have provided informed assent and parental consent will be included in the study. Teachers and parents will be recruited a month before follow-up. As part of the recruitment process, an information sheet will be provided and informed consent will be sought. Once written consent is obtained, teachers and parents will be recruited into the study.

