### Randomization

Schools within each country will be randomly allocated to control or intervention arm using Microsoft excel (Microsoft 365) RAND function. Allocation will remain for the duration of the project.

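### The 80% power stated for each country takes no account of there being only about 6 randomised schools per country; a valid school-level comparison has roughly 56–65%

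*Protocol article*

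**What the plan says.** The Power section gives these elements:

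- Target: "The sample size was calculated to achieve 80% power".
- Starting level: "assuming baseline knowledge of 30 percentage points".
- Clustering: "a design effect of 2 to account for cluster sampling".
- Loss to follow-up: "Accounting for 10% attrition".
- Result: "it was estimated that a total of 227 participants would be needed to detect a difference of 5 percentage points in knowledge".

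The result is rounded up to 228 and applied country by country: "114 in intervention arm, 114 in control arm) in each country".

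The number of schools appears only under Consent and Recruitment, where it follows from the pupil target: "approximately 6 schools will be selected in each country to achieve a total sample size of 228 per country". Under Randomization the unit is the school and the stratum is the country: "Schools within each country will be randomly allocated to control or intervention arm". The Data Analysis section names generalised estimating equations (GEE) to handle clustering and repeated measures. It describes no test within a single country.

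**The concern.** A design effect enlarges the variance of the arm means because pupils in one school resemble each other. It does not allow for the between-school variance having to be estimated from very few schools. With about 3 schools per arm that second penalty is large: the two-sided 5% critical value is 2.78, not 1.96.

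The article attaches 80% power to a sample that it sets separately for each country, so a reader will take each country as able to show a 5-point effect four times in five. If the true figure is nearer 56%, a real 5-point effect would be missed in a given country more than four times in ten. The results are meant to inform scale-up in three countries, and a non-significant result in one of them could be read as absence of benefit.

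**Working it through.** **Inputs from the article.** Difference 5 points; power 80%; design effect (DE) 2; attrition 10%; 228 enrolled per country, 114 per arm; about 6 schools per country.

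**Inputs assumed.** Two-sided 5% alpha (the article states this level only for the Shapiro-Wilk test); 3 schools per arm (inferred from 6 schools and equal arms); SD of the knowledge score, back-solved below.

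**Step 1: reproduce 227.** For two means with normal quantiles, n per arm = 2 × SD² × (1.960 + 0.842)² / 5².

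- With SD 9: 2 × 81 × 7.849 / 25 = 50.9, so 51 per arm.
- Times 2 arms and DE 2: 204.
- Divided by 0.9: 226.7, so 227, as stated.

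Read instead as proportions (30% against 35%), the total would be about 6,100, so the calculation must be for means. One-sided 5% with SD 10.1 also gives 227.

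**Step 2: noncentrality.** A normal-quantile calculation at 80% power fixes difference/SE at 1.960 + 0.842 = 2.80, whatever the SD. Directly, with 228 enrolled:

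- Analysed per arm: 228 × 0.9 / 2 = 102.6; effective number 102.6 / 2 = 51.3.
- SE with SD 9: 9 × √(2/51.3) = 1.777; 5 / 1.777 = 2.81.

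**Step 3: power with the degrees of freedom of the design.** With 6 schools in two arms, df = 6 − 2 = 4. Noncentral t power:

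| Setting, one country | df | Power for 5 points |
|---|---|---|
| Normal quantiles, as in Step 1 | – | 80% |
| 3 v 3 schools, two-sided 5% | 4 | 56% |
| 4 v 4 schools, DE held at 2 | 6 | 65% |
| 4 v 4 schools, 228 pupils, intraclass correlation held at 0.030 (DE 1.74) | 6 | 71% |
| 3 v 3 schools, one-sided 5% (noncentrality 2.49) | 4 | 66% |

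Simulating school means for 3 v 3 with SD 9 gives 56.6%, with type I error 5.0%.

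**Step 4: detectable difference.** 80% power at 4 df needs noncentrality 3.76, so 5 × 3.76 / 2.80 = 6.7 points.

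**Step 5: pooled comparison.** With three countries the noncentrality is 2.80 × √3 = 4.85. With 18 schools, three country terms and one arm term, df = 14. Power for 5 points is 99%. 80% power needs noncentrality 3.01, so the detectable difference is 5 × 3.01 / 4.85 = 3.1 points.

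**The case against.** - **No per-country test is described.** The analysis section compares intervention with control schools and is silent on country, and the hypothesis is a single one. This stands, and it limits the harm to how country results are used. It does not remove the point, because the Power section itself sets the sample for each country.
- **GEE already handles clustering.** It does with many clusters. In simulation with 6 schools, uncorrected normal-based tests kept apparent power of 79% to 87% only with type I error of about 12% to 19%. That does not rescue 80% at a valid 5% level.
- **The SD is not a plan input.** This stands. The SD cancels in Step 2 only if normal quantiles were used. A calculation that already used 4 df with an SD of about 6.7 would also be consistent with the stated sample. The normal-quantile reading is the more natural: a round SD of 9 returns 227 exactly, and the school count was set afterwards to reach the pupil target.
- **The school count is approximate.** This stands: 56% is one point in a range.
- **Baseline adjustment would help.** If it removes variance equivalent to a correlation of 0.5 (assumed), power is about 59% to 68% (3 or 4 df). At 0.7 it is about 74% to 83%. So 80% is reached only at the favourable end, and the article's calculation takes no credit for it.

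A reader might also infer that the trial as a whole is underpowered. The documents do not support that, since the pooled comparison has ample power on the same inputs. Nor is the absence of an SD, an intraclass correlation or a named primary model an error in itself: an article commonly leaves these to the full protocol or analysis plan.

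**Conclusion.** The point holds for the power stated per country, and should be fixed; it does not put the trial at risk. The figure of 227 is sound arithmetic for a normal-quantile calculation with SD 9, but the 80% attached to it is not what about 6 randomised schools deliver. Under two-sided 5% alpha and 3 v 3 schools, per-country power for 5 points is about 56%, with about 6.7 points detectable at 80%. It is about 65% with 8 schools at an unchanged design effect and about 66% at one-sided 5%. An uneven split of 6 schools would lower it.

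The conclusion rests on the assumed alpha, the inferred split and the reading that normal quantiles were used. It would be tempting to present 56% as following from the plan's stated inputs alone, or to say that the plan will test each country separately; the article supports neither.

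**What to change.** Amend the Power section in one of two ways:

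1. Keep the per-country statement, but give the power as roughly 56–65% for 5 points, with the assumed alpha, SD, design effect and number of schools per arm beside it.
2. Attach the power claim to the pooled, country-stratified comparison over about 18 schools: about 99% for 5 points and about 3.1 points detectable at 80%, on the same inputs. State the SD used, because this figure does depend on it: at an assumed SD of 15, pooled power is 78%.

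In either case, present country-specific effects as estimates with confidence intervals that use a small-sample, t-based correction for the number of schools, and do not read a non-significant result in one country as no effect.

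The cost is one rewritten paragraph and a less favourable per-country figure. No schools or pupils need to be added, so the change is feasible although the trial is already running in Lao PDR and Thailand.

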## Results

The trial is in progress in Lao PDR and Thailand and is expected to commence in Cambodia in January 2024. Study results are expected to be available 18 months from the start of recruitment and will be submitted for publication thereafter.

## Discussion

This study was designed to assess the acceptability of the MGO and MGLM cartoon packages, and to evaluate the impact of these packages on schoolchildren’s KAP on OV and STH infection, respectively, in Cambodia, Thailand and Lao PDR. The expected outcomes are initial and sustained acceptability of the MGO and MGLM cartoon packages and improved KAP on OV and STH infection among intervention students. Several studies have outlined the importance of child-targeted health education interventions to improve health knowledge and behavior and prevent disease [26-28]. This is particularly important for populations at-risk of diseases such as OV and STH, which can have long-term health and developmental impacts [14-18]. Previous “Magic Glasses” studies have demonstrated the effectiveness of a school-based educational cartoon in improving KAP among schoolchildren in China and Philippines, and reducing the STH burden [30,31]. The “Magic Glasses Philippines” demonstrated the generalizability of “Magic Glasses” to other regions with endemic infectious diseases [30]. This trial will provide insight on the translatability of “Magic Glasses” to other infectious diseases with different methods of transmission and prevention. In addition, this will be the first study to formally assess the acceptability of “Magic Glasses” intervention.

This study does have some limitations. First, this study relies on self-reported data from children, which could lead to measurement error. Schoolchildren’s self-reported OV and STH behavior in particular, may be misrepresented due to social desirability bias. However, several studies have supported child self-reporting as a valid and reliable measure in health research [44-46]. Second, while children receiving the intervention will learn how to prevent OV transmission by adequately cooking freshwater cyprinid fish, it is possible that they will not be able to do this, due to parental control over household food preparation. For this reason, we will also investigate the indirect impact of the intervention on parents’ KAP relating to OV and STH infection. Second, due to the nature of the study, it was not possible to blind participants or research staff. Therefore, it is possible that nonblinding bias could occur.

It is expected that the acceptability and KAP findings will provide evidence for the scalability of the “Magic Glasses: Lower Mekong” and “Magic Glasses: Opisthorchiasis” interventions for Cambodia, Lao PDR, and Thailand and more broadly, provide further support for the “Magic Glasses” intervention. These findings have implications for the expansion of the “Magic Glasses” to other infectious diseases and countries, as a novel, engaging and cost-effective tool in school-based health education.

## Appendix

Multimedia Appendix 1 Anticipated delivery dates for baseline, intervention delivery, reinforcement and follow-up for the “Magic Glasses Lower Mekong” and “Magic Glasses Opisthorchiasis” cluster randomized controlled trial in Cambodia, Lao PDR, and Thailand.

Multimedia Appendix 2 Opisthorchis viverrini knowledge, attitudes, and practices questionnaire for the “Magic Glasses Lower Mekong” and “Magic Glasses Opisthorchiasis” cluster randomized controlled trial.

Multimedia Appendix 3 Soil-transmitted helminths knowledge, attitudes, and practices questionnaire for the “Magic Glasses Lower Mekong” and “Magic Glasses Opisthorchiasis” cluster randomized controlled trial.

Multimedia Appendix 4 Magic Glasses Opisthorchiasis acceptability questionnaire for the “Magic Glasses Lower Mekong” and “Magic Glasses Opisthorchiasis” cluster randomized controlled trial.

Multimedia Appendix 5 Magic Glasses Lower Mekong acceptability questionnaire for the “Magic Glasses Lower Mekong” and “Magic Glasses Opisthorchiasis” cluster randomized controlled trial.

## Abbreviations

cRCT: cluster randomized controlled trial
FGD: focus group discussion
KAP: knowledge, attitudes, and practices
KII: key informant interviews
LMB: Lower Mekong Basin
MDA: mass drug administration
MGLM: Magic Glasses Lower Mekong
MGO: Magic Glasses Opisthorchiasis
OV: Opisthorchis viverrini
PDR: People’s Democratic Republic
SAC: school-aged children
STH: soil-transmitted helminths
TFA: Theoretical Framework of Acceptability
WASH: water, sanitation, and hygiene
WHO: World Health Organization
